### Putative Secondary outcomes

Change from baseline in each continuous secondary outcome measure will be analysed in a linear regression analysis predicting change from baseline from randomised intervention group adjusting for baseline value of the outcome measure, child age and gender.

Binary secondary outcome measures (ECBI problem score > 11 and ECBI intensity score > 127) will be analysed in a logistic regression analysis predicting the outcome from randomised intervention group adjusting for baseline ECBI problem score or ECBI intensity score (as continuous measures), child age and gender.

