# Introduction

## Study Background

Attention Deficit/Hyperactivity Disorder (ADHD) substantially burdens affected children, parents and society. It is well-known that early drug therapies can change trajectories and reduce individual, family and societal burden, and cost‐effectiveness studies have focused on available drug therapies and less on non‐medical interventions. Children with neurodevelopmental problems such as ADHD are at higher risk of experiencing abuse and/or neglect so it is crucial that their families receive targeted support. As a first line of treatment, NICE guidelines recommend a group parenting intervention, the effectiveness of which has been proven. It is however unclear whether an intervention designed specifically for families of children with a diagnosis will be more effective and cost effective.

Parents In Control (Parents InC / PInC) offers support designed specifically for parents of children with ADHD. The current best evidenced alternative is Incredible Years (IY). What needs to be determined is whether PInC i) is at least as effective as IY in impacting children’s behaviour outcomes; ii) is cost‐effective; and iii) offers something unique in terms of parenting self‐competence and quality of life.

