### Secondary Outcomes

The proposed secondary outcomes for a full trial are

- Eyberg Child Behaviour Inventory (ECBI) problem score > 11 / intensity score > 127
- Strength and Difficulties Questionnaire (SDQ) total score
- General Health Questionnaire (GHQ)
- Parental ADHD symptoms measured using the ADHD Rating Scale (ASRS-v1.1) Part A and Part B
- Parenting stress measured using the Parenting Daily Hassles Scale (PDHS) challenging behaviour intensity and frequency , parenting tasks frequency and intensity
- Goal Based Outcomes from the Child Outcomes Research Consortium (CORC-GBO) – amount of movement along the scale from baseline to follow-up
- Parent quality of life measured using the EQ-5D-5L (health utility score and VAS)
- Child quality of life measured using the PedsQL total score, psychosocial health summary score, physical health summary score
- Service use

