### General Principles

Rates will be calculated with Clopper-Pearson^1^ 95% confidence intervals.

Proposed primary and secondary outcome measures will be summarised at baseline and follow up, and separately by follow-up time point (12 months for recruitment waves 1 to 3, 6 months for recruitment wave 4). Changes from baseline in the proposed outcome measures will be summarised in the same way. All summaries will include the number of observed values and the number of missing values. Continuous variables will be summarised by the mean, standard deviation, median, interquartile range, minimum and maximum. Categorical variables will be summarised as the number and percentage of participants in each group.

The primary and numeric secondary efficacy outcomes will be compared between intervention groups using linear regression analyses predicting change in outcome from intervention group, adjusting for baseline value of the outcome, age and gender.

Binary secondary efficacy outcomes will be compared between intervention groups using logistic regression analyses predicting outcome from intervention group, adjusting for age and gender.

If numbers are too low for the planned regression analysis, unadjusted regression analyses or simple tests will be carried out instead. For numbers below five in any group, no statistical tests will be carried out.

The distribution of the residuals of each linear regression analysis will be reviewed and transformations will be applied to the outcome variable as appropriate.

Regression results will be reported as adjusted mean difference between intervention groups, or adjusted odds ratios for logistic regressions, with 95% confidence interval and p-value.

Missing values will not be imputed.

Health economic analyses will be carried out by health economists and are not part of this SAP.

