### Additional Analyses

No additional analyses planned.

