| Change from baseline | Mean (SD)  Median (IQR)  [Range] | xx.x (xx.x)  xx.x (xx.x, xx.x)  [xx.x, xx.x] | xx.x (xx.x)  xx.x (xx.x, xx.x)  [xx.x, xx.x] | xx.x (xx.x)  xx.x (xx.x, xx.x)  [xx.x, xx.x] |
| Linear regression analysis predicting change from baseline from randomised intervention group adjusting for baseline PSOC, child age and gender | | | | |
|  |  | Adjusted mean difference (95% confidence interval) | | p-value |
| IY vs. PInC | | x.xx (x.xx, x.xx) | | x.xxxx |
| Residual standard deviation | | x.xx | |  |

Table 3.2 Primary outcome - PSOC. ITT population with 12-month follow-up.

|  |  |  | Randomised intervention | |
| --- | --- | --- | --- | --- |
|  |  | All | PInC | IY |
| Baseline | N_OBS_ (N_MISS_)  Mean (SD)  Median (IQR)  [Range] | nn (nn)  xx.x (xx.x)  xx.x (xx.x, xx.x)  [xx.x, xx.x] | nn (nn)  xx.x (xx.x)  xx.x (xx.x, xx.x)  [xx.x, xx.x] | nn (nn)  xx.x (xx.x)  xx.x (xx.x, xx.x)  [xx.x, xx.x] |
| Follow-up | N_OBS_ (N_MISS_)  Mean (SD)  Median (IQR)  [Range] | nn (nn)  xx.x (xx.x)  xx.x (xx.x, xx.x)  [xx.x, xx.x] | nn (nn)  xx.x (xx.x)  xx.x (xx.x, xx.x)  [xx.x, xx.x] | nn (nn)  xx.x (xx.x)  xx.x (xx.x, xx.x)  [xx.x, xx.x] |
| Participants with baseline and follow-up data only | | | | |
| N |  | nn | nn | nn |
| Baseline | Mean (SD)  Median (IQR)  [Range] | xx.x (xx.x)  xx.x (xx.x, xx.x)  [xx.x, xx.x] | xx.x (xx.x)  xx.x (xx.x, xx.x)  [xx.x, xx.x] | xx.x (xx.x)  xx.x (xx.x, xx.x)  [xx.x, xx.x] |
| Follow-up | Mean (SD)  Median (IQR)  [Range] | xx.x (xx.x)  xx.x (xx.x, xx.x)  [xx.x, xx.x] | xx.x (xx.x)  xx.x (xx.x, xx.x)  [xx.x, xx.x] | xx.x (xx.x)  xx.x (xx.x, xx.x)  [xx.x, xx.x] |
| Change from baseline | Mean (SD)  Median (IQR)  [Range] | xx.x (xx.x)  xx.x (xx.x, xx.x)  [xx.x, xx.x] | xx.x (xx.x)  xx.x (xx.x, xx.x)  [xx.x, xx.x] | xx.x (xx.x)  xx.x (xx.x, xx.x)  [xx.x, xx.x] |
| Linear regression analysis predicting change from baseline from randomised intervention group adjusting for baseline PSOC, child age and gender | | | | |
|  |  | Adjusted mean difference (95% confidence interval) | | p-value |
| IY vs. PInC | | x.xx (x.xx, x.xx) | | x.xxxx |
| Residual standard deviation | | x.xx | |  |

Table 3.3 Primary outcome - PSOC. PP population.

|  |  |  | Intervention received | |
| --- | --- | --- | --- | --- |
|  |  | All | PInC | IY |

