| Baseline | N_OBS_ (N_MISS_)  Mean (SD)  Median (IQR)  [Range] | nn (nn)  xx.x (xx.x)  xx.x (xx.x, xx.x)  [xx.x, xx.x] | nn (nn)  xx.x (xx.x)  xx.x (xx.x, xx.x)  [xx.x, xx.x] | nn (nn)  xx.x (xx.x)  xx.x (xx.x, xx.x)  [xx.x, xx.x] |
| Follow-up | N_OBS_ (N_MISS_)  Mean (SD)  Median (IQR)  [Range] | nn (nn)  xx.x (xx.x)  xx.x (xx.x, xx.x)  [xx.x, xx.x] | nn (nn)  xx.x (xx.x)  xx.x (xx.x, xx.x)  [xx.x, xx.x] | nn (nn)  xx.x (xx.x)  xx.x (xx.x, xx.x)  [xx.x, xx.x] |
| Participants with baseline and follow-up data only | | | | |
| N |  | nn | nn | nn |
| Baseline | Mean (SD)  Median (IQR)  [Range] | xx.x (xx.x)  xx.x (xx.x, xx.x)  [xx.x, xx.x] | xx.x (xx.x)  xx.x (xx.x, xx.x)  [xx.x, xx.x] | xx.x (xx.x)  xx.x (xx.x, xx.x)  [xx.x, xx.x] |
| Follow-up | Mean (SD)  Median (IQR)  [Range] | xx.x (xx.x)  xx.x (xx.x, xx.x)  [xx.x, xx.x] | xx.x (xx.x)  xx.x (xx.x, xx.x)  [xx.x, xx.x] | xx.x (xx.x)  xx.x (xx.x, xx.x)  [xx.x, xx.x] |
| Change from baseline | Mean (SD)  Median (IQR)  [Range] | xx.x (xx.x)  xx.x (xx.x, xx.x)  [xx.x, xx.x] | xx.x (xx.x)  xx.x (xx.x, xx.x)  [xx.x, xx.x] | xx.x (xx.x)  xx.x (xx.x, xx.x)  [xx.x, xx.x] |
| Linear regression analysis predicting change from baseline from randomised intervention group adjusting for baseline PSOC, child age and gender | | | | |
|  |  | Adjusted mean difference (95% confidence interval) | | p-value |
| IY vs. PInC | | x.xx (x.xx, x.xx) | | x.xxxx |
| Residual standard deviation | | x.xx | |  |

Table 4.1.1 Secondary outcome – ECBI problem score. ITT population.

|  |  |  | Intervention received | |
| --- | --- | --- | --- | --- |
|  |  | All | PInC | IY |
| Baseline | N_OBS_ (N_MISS_)  N (%) ≤ 11  N (%) > 11 | nn (nn)  nn (xx.x)  nn (xx.x) | nn (nn)  nn (xx.x)  nn (xx.x) | nn (nn)  nn (xx.x)  nn (xx.x) |
| Follow-up | N_OBS_ (N_MISS_)  N (%) ≤ 11  N (%) > 11 | nn (nn)  nn (xx.x)  nn (xx.x) | nn (nn)  nn (xx.x)  nn (xx.x) | nn (nn)  nn (xx.x)  nn (xx.x) |
| Participants with baseline and follow-up data only | | | | |
| N |  | nn | nn | nn |
| Baseline | N_OBS_ (N_MISS_)  N (%) ≤ 11  N (%) > 11 | nn (nn)  nn (xx.x)  nn (xx.x) | nn (nn)  nn (xx.x)  nn (xx.x) | nn (nn)  nn (xx.x)  nn (xx.x) |
| Follow-up | N_OBS_ (N_MISS_)  N (%) ≤ 11  N (%) > 11 | nn (nn)  nn (xx.x)  nn (xx.x) | nn (nn)  nn (xx.x)  nn (xx.x) | nn (nn)  nn (xx.x)  nn (xx.x) |
| Logistic regression analysis predicting change from baseline from randomised intervention group adjusting for baseline ECBI problem score > 11, child age and gender | | | | |

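### ECBI is analysed only as above or below a cut-off; add the numeric problem and intensity scores as outcomes and report their SDs

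*Supplement*

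**What the plan says.** - **Outcome definition.** The SAP's Secondary Outcomes list gives ECBI only in cut-off form: "Eyberg Child Behaviour Inventory (ECBI) problem score > 11 / intensity score > 127". SDQ total score, next in the list, has no cut-off.
- **Analysis.** Putative Secondary outcomes (3.4.2) gives every continuous secondary measure a linear regression on change. ECBI is instead handled thus: "Binary secondary outcome measures (ECBI problem score > 11 and ECBI intensity score > 127) will be analysed in a logistic regression analysis", "adjusting for baseline ECBI problem score or ECBI intensity score (as continuous measures), child age and gender".
- **Anything else on ECBI.** Additional Analyses (3.4.3) reads "No additional analyses planned".
- **Table shells.** Table 4.1.1 (problem score) has counts and percentages at or below 11 and above 11, then an odds ratio. Tables 4.1.2, 4.2.1 and 4.2.2 are titles only. By contrast, Table 3.1 for PSOC has means, SDs, change from baseline and a row for "Residual standard deviation".
- **General rule.** General Principles says "Continuous variables will be summarised by the mean, standard deviation, median, interquartile range, minimum and maximum", but ECBI is never listed as a continuous outcome, so the rule does not clearly reach it.
- **Background.** One of the things to be determined is whether PInC is "at least as effective as IY in impacting" child behaviour outcomes. No instrument is named there.

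**The concern.** The SAP keeps the full ECBI score as a predictor and discards it as the outcome, without giving a reason. This has three consequences.

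1. **Precision.** A dichotomy records only whether a child is above the cut-off. A child who improves substantially but stays on the same side counts as unchanged.
2. **Stability.** An adjusted logistic model with four slopes on about 40 families is fragile if most children score on one side of the cut-off, which is plausible in a sample diagnosed with ADHD.
3. **Planning.** A feasibility trial is a natural source of the SDs that a full trial needs. If child behaviour is to help size that trial, as the background question suggests it might, the planned output contains no ECBI SD.

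**Working it through.** **Sample size (SAP, Sample Size and Power).** 100 approached × 0.60 × 2/3 = 40 families, or 20 per arm. This reproduces the plan's figure. The SAP gives no power calculation, effect size or margin.

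**Assumed, because the documents do not say.** Normal scores; 50% to 90% of children above the cut-off; baseline to follow-up correlation ρ of 0 to 0.7; and, for illustration, a 0.5 SD difference, two-sided 5% level and 80% power.

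**Information kept by the dichotomy.** With share p above the cut-off, relative efficiency = φ(z_p)² / [p(1 − p)].

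| Share above | φ(z_p)² | p(1 − p) | Kept | Lost | Equivalent families of 40 |
| --- | --- | --- | --- | --- | --- |
| 50% | 0.1592 | 0.25 | 0.64 | 36% | 40 × 0.637 ≈ 25 |
| 70% | 0.1209 | 0.21 | 0.58 | 42% | 40 × 0.576 ≈ 23 |
| 80% | 0.0784 | 0.16 | 0.49 | 51% | 40 × 0.490 ≈ 20 |
| 90% | 0.0308 | 0.09 | 0.34 | 66% | 40 × 0.342 ≈ 14 |

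Under normality, about a third is the smallest possible loss. Adjusting both analyses for the continuous baseline widens the gap. In a large simulation (probit against linear regression), the loss for 50% to 80% above was 43% to 56% at ρ = 0.5 and 52% to 63% at ρ = 0.7.

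**The same loss as sample size and power (0.5 SD, unadjusted).** The numeric score needs 63 per arm. The dichotomy needs 102, 103, 115 and 152 at 50, 70, 80 and 90% above. At 20 per arm, power is 35% for the numeric score against 23, 23, 21 and 17%.

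**The same loss as an expected z (40 families).** For baseline-adjusted linear regression, z = 0.5 / √[(1 − ρ²) × 4/40]. This is 0.5/0.274 = 1.8 at ρ = 0.5 and 0.5/0.226 = 2.2 at ρ = 0.7. In simulation the logistic model averaged about 1.35 at a 50% split and 1.0 to 1.1 at 80% above, counting usable fits only.

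**Stability of the logistic model.** The slopes are arm, baseline score, age and gender. At 80% above, 40 × 0.20 = 8 children are at or below the cut-off, which is 8/4 = 2 per slope and 20 × 0.20 = 4 per arm. In simulated trials of 40 families (0.5 SD effect, ρ 0.5 to 0.7), the fit failed or gave extreme coefficients in 9% to 14% at 75% above and 31% to 37% at 85%. These rates depend on what counts as extreme. Counting only non-convergence, or a coefficient or standard error beyond 10, a further run gave 4% to 7% and 21% to 28%. The direction is clear; the exact rate is not.

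**What an ECBI SD from this trial would be worth.** With 38 degrees of freedom, the 95% limits are √(38/χ²) times the estimate, or 0.82 to 1.29 times. That is imprecise but usable for planning.

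**The baseline term in the logistic model, side by side.** General Principles adjusts binary outcomes for age and gender only. Section 3.4.2 uses "adjusting for baseline ECBI problem score or ECBI intensity score (as continuous measures), child age and gender". Table 4.1.1 uses "adjusting for baseline ECBI problem score > 11, child age and gender". These are three different models.

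**The case against.** The strongest case against runs as follows.

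- **This is a feasibility trial.** Its research questions concern willingness to be randomised, recruitment, retention and acceptability. No efficacy comparison is powered, and even the numeric analysis has only about 35% power for 0.5 SD unadjusted. This stands, and it limits the importance of the point. But the SAP plans efficacy comparisons with intervals and p-values anyway, and they should not be less precise than the data allow.
- **The SAP has a safeguard.** General Principles falls back to unadjusted regression or simple tests when numbers are too low, and to no test below five in any group. This answers much of the instability worry. It restores no precision, and if the below-five rule is read as covering outcome cells, the 4 per arm expected at 80% above could leave ECBI with no comparison.
- **The cut-offs may aid clinical reading.** This stands, and is why they should be kept.
- **The protocol is not shown.** It may itself set the cut-off outcomes. That favours adding the numeric scores over replacing the cut-offs.

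A reader might infer more than the documents support:

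- **That ECBI is the main child-behaviour measure.** No section says so. It is one of several proposed secondary outcomes, and SDQ total is analysed as a number.
- **That the full trial is left without an SD.** PSOC is the proposed primary outcome, with a residual SD in Table 3.1, and SDQ falls under the general rule for continuous variables. Only the ECBI SD is absent from the planned output, and it can be computed from scores already held.
- **That every other scale is certain to get a regression.** The text of 3.4.2 implies it, but the CORC-GBO shell (Table 4.11.1) contains none.

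**Conclusion.** The point holds as a moderate one. ECBI is analysed only as two dichotomies, although the numeric scores are available, and no planned ECBI table is shown to give a mean, SD, change or residual SD. Under normality the loss is 36% of the information with half the children above the cut-off, 51% at 80% above and 66% at 90% above, and more with adjustment for a correlated baseline. To say flatly that a third to a half is lost would go beyond the documents, which give neither the distribution nor the shares; the loss could exceed a half. With about 40 families the adjusted logistic model may be unstable, and the fallback rule protects against a bad fit without recovering precision. The missing SD is a gap in reporting that matters mainly if child behaviour is to help size the full trial. No feasibility conclusion is affected.

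**What to change.** 1. In Secondary Outcomes and in 3.4.2, add the numeric ECBI problem and intensity scores as outcomes. Analyse each by linear regression on change from baseline, adjusted for baseline score, child age and child gender.
2. In Tables 4.1.1, 4.1.2, 4.2.1 and 4.2.2, report mean, SD, change from baseline and residual SD in the layout of Table 3.1.
3. Keep the proportions above 11 and above 127 as a supplementary summary or logistic model. If the model is kept, use the continuous baseline of 3.4.2 throughout, and align General Principles and Table 4.1.1 with it.
4. If the protocol defines ECBI only by the cut-offs, record the numeric analysis in the SAP section on analyses additional to the protocol, which at present declares none.

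The cost is SAP wording, four table shells and a little more analysis. No new data are needed.

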### Additional Analyses

No additional analyses planned.

### Subgroup Analyses

To assess the impact of the follow-up time on the proposed primary and secondary outcomes, the analysis will be repeated in those participants who have 12-month follow-up only.

### Sensitivity Analyses

The following measures will be taken at baseline and repeated prior to starting the intervention if the waiting time exceeds 3 months, to assess to what extent baseline measures are changing over time and how this affects the results:

- SDQ
- PDHS
- GBO
- EQ-5D-5L

As a sensitivity analysis, the secondary analyses relating to those outcomes will be repeated using the repeat baseline measure instead of the baseline measure.

### Per protocol analysis

The analysis of the primary outcome will be repeated using treatment received instead of allocated treatment in the PP population.

## Safety Outcomes

### Treatment Compliance

Group attendance will be summarised overall and by intervention group.

### Premature Withdrawal

Withdrawals and withdrawal reasons will be summarised overall and by intervention group.

### Adverse Events

Information is collected on Serious Adverse Events only. The number of participants experiencing at least one SAE will be summarised overall and by intervention group. SAE characteristics (seriousness criteria, severity, expectedness, relation to intervention, outcome, duration) will be summarised overall and by study group. All SAEs will be listed.

### Concomitant Medications

Parent and child medication use will be summarised overall and by intervention group at baseline and follow-up for medications of interest. These will be specified prior to the final analysis.

# Data Conventions

A separate assumptions document named SPARCLAR_Assumptions_vx_x.docx detailing data rules (e.g. partial dates) will be agreed prior to database lock.

# Document History

This is version 1.0 of the SAP for the SPARCLAR study, its initial creation, dated 28/10/2020.

# Table Templates

Table 1.1 Recruitment. Proportions reported in % with 95% confidence interval.

|  | N | Proportion |
| --- | --- | --- |
| Eligible subjects in research period | nn |  |
| Approached subjects (out of all eligible subjects) | nn | xx.x (xx.x – xx.x) |
| Subjects consented (out of all subjects approached) | nn | xx.x (xx.x – xx.x) |
| Subjects consented with baseline data (out of all subjects approached) | nn | xx.x (xx.x – xx.x) |

Table 1.2 Retention. Proportions are out of all who consented and have any baseline data (ITT population), reported in % with 95% confidence interval.

|  |  | | Randomised intervention | | | |
| --- | --- | --- | --- | --- | --- | --- |
|  | All | | PInC | | IY | |
|  | N | Proportion | N | Proportion | N | Proportion |
| Randomised | nn |  | nn |  | Nn |  |
| Provide any follow-up data | nn | xx.x (xx.x – xx.x) | nn | xx.x (xx.x – xx.x) | nn | xx.x (xx.x – xx.x) |
| Provide follow-up data for |  |  |  |  |  |  |
| PSOC | nn | xx.x (xx.x – xx.x) | nn | xx.x (xx.x – xx.x) | nn | xx.x (xx.x – xx.x) |
| ECBI problem score | nn | xx.x (xx.x – xx.x) | nn | xx.x (xx.x – xx.x) | nn | xx.x (xx.x – xx.x) |
| ECBI intensity score | nn | xx.x (xx.x – xx.x) | nn | xx.x (xx.x – xx.x) | nn | xx.x (xx.x – xx.x) |
| SDQ | nn | xx.x (xx.x – xx.x) | nn | xx.x (xx.x – xx.x) | nn | xx.x (xx.x – xx.x) |
| GHQ | nn | xx.x (xx.x – xx.x) | nn | xx.x (xx.x – xx.x) | nn | xx.x (xx.x – xx.x) |
| ASRS (parent) Part A | nn | xx.x (xx.x – xx.x) | nn | xx.x (xx.x – xx.x) | nn | xx.x (xx.x – xx.x) |
| ASRS (parent) Part B | nn | xx.x (xx.x – xx.x) | nn | xx.x (xx.x – xx.x) | nn | xx.x (xx.x – xx.x) |
| PDHS challenging behaviour intensity | nn | xx.x (xx.x – xx.x) | nn | xx.x (xx.x – xx.x) | nn | xx.x (xx.x – xx.x) |
| PDHS challenging behaviour frequency | nn | xx.x (xx.x – xx.x) | nn | xx.x (xx.x – xx.x) | nn | xx.x (xx.x – xx.x) |
| PDHS parenting tasks intensity | nn | xx.x (xx.x – xx.x) | nn | xx.x (xx.x – xx.x) | nn | xx.x (xx.x – xx.x) |
| PDHS parenting tasks frequency | nn | xx.x (xx.x – xx.x) | nn | xx.x (xx.x – xx.x) | nn | xx.x (xx.x – xx.x) |
| CORC-GBO | nn | xx.x (xx.x – xx.x) | nn | xx.x (xx.x – xx.x) | nn | xx.x (xx.x – xx.x) |
| EQ-5D-5L | nn | xx.x (xx.x – xx.x) | nn | xx.x (xx.x – xx.x) | nn | xx.x (xx.x – xx.x) |
| PedsQL psychosocial health summary score | nn | xx.x (xx.x – xx.x) | nn | xx.x (xx.x – xx.x) | nn | xx.x (xx.x – xx.x) |
| PedsQL physical health summary score | nn | xx.x (xx.x – xx.x) | nn | xx.x (xx.x – xx.x) | nn | xx.x (xx.x – xx.x) |
| PedsQL total score | nn | xx.x (xx.x – xx.x) | nn | xx.x (xx.x – xx.x) | nn | xx.x (xx.x – xx.x) |

Table 1.3 Retention – waves 1-3. Proportions are out of all who consented and have any baseline data (ITT population), reported in % with 95% confidence interval.

|  |  | | Randomised intervention | | | |
| --- | --- | --- | --- | --- | --- | --- |
|  | All | | PInC | | IY | |
|  | N | Proportion | N | Proportion | N | Proportion |
| Randomised | nn |  | nn |  | Nn |  |
| Provide any follow-up data | nn | xx.x (xx.x – xx.x) | nn | xx.x (xx.x – xx.x) | nn | xx.x (xx.x – xx.x) |
| Provide follow-up data for |  |  |  |  |  |  |
| PSOC | nn | xx.x (xx.x – xx.x) | nn | xx.x (xx.x – xx.x) | nn | xx.x (xx.x – xx.x) |
| ECBI problem score | nn | xx.x (xx.x – xx.x) | nn | xx.x (xx.x – xx.x) | nn | xx.x (xx.x – xx.x) |
| ECBI intensity score | nn | xx.x (xx.x – xx.x) | nn | xx.x (xx.x – xx.x) | nn | xx.x (xx.x – xx.x) |
| SDQ | nn | xx.x (xx.x – xx.x) | nn | xx.x (xx.x – xx.x) | nn | xx.x (xx.x – xx.x) |
| GHQ | nn | xx.x (xx.x – xx.x) | nn | xx.x (xx.x – xx.x) | nn | xx.x (xx.x – xx.x) |
| ASRS (parent) Part A | nn | xx.x (xx.x – xx.x) | nn | xx.x (xx.x – xx.x) | nn | xx.x (xx.x – xx.x) |
| ASRS (parent) Part B | nn | xx.x (xx.x – xx.x) | nn | xx.x (xx.x – xx.x) | nn | xx.x (xx.x – xx.x) |
| PDHS challenging behaviour intensity | nn | xx.x (xx.x – xx.x) | nn | xx.x (xx.x – xx.x) | nn | xx.x (xx.x – xx.x) |
| PDHS challenging behaviour frequency | nn | xx.x (xx.x – xx.x) | nn | xx.x (xx.x – xx.x) | nn | xx.x (xx.x – xx.x) |
| PDHS parenting tasks intensity | nn | xx.x (xx.x – xx.x) | nn | xx.x (xx.x – xx.x) | nn | xx.x (xx.x – xx.x) |
| PDHS parenting tasks frequency | nn | xx.x (xx.x – xx.x) | nn | xx.x (xx.x – xx.x) | nn | xx.x (xx.x – xx.x) |
| CORC-GBO | nn | xx.x (xx.x – xx.x) | nn | xx.x (xx.x – xx.x) | nn | xx.x (xx.x – xx.x) |
| EQ-5D-5L | nn | xx.x (xx.x – xx.x) | nn | xx.x (xx.x – xx.x) | nn | xx.x (xx.x – xx.x) |
| PedsQL psychosocial health summary score | nn | xx.x (xx.x – xx.x) | nn | xx.x (xx.x – xx.x) | nn | xx.x (xx.x – xx.x) |
| PedsQL physical health summary score | nn | xx.x (xx.x – xx.x) | nn | xx.x (xx.x – xx.x) | nn | xx.x (xx.x – xx.x) |
| PedsQL total score | nn | xx.x (xx.x – xx.x) | nn | xx.x (xx.x – xx.x) | nn | xx.x (xx.x – xx.x) |

Table 1.4 Retention – wave 4. Proportions are out of all who consented and have any baseline data (ITT population), reported in % with 95% confidence interval.

|  |  | | Randomised intervention | | | |
| --- | --- | --- | --- | --- | --- | --- |
|  | All | | PInC | | IY | |
|  | N | Proportion | N | Proportion | N | Proportion |
| Randomised | nn |  | nn |  | Nn |  |
| Provide any follow-up data | nn | xx.x (xx.x – xx.x) | nn | xx.x (xx.x – xx.x) | nn | xx.x (xx.x – xx.x) |
| Provide follow-up data for |  |  |  |  |  |  |
| PSOC | nn | xx.x (xx.x – xx.x) | nn | xx.x (xx.x – xx.x) | nn | xx.x (xx.x – xx.x) |
| ECBI problem score | nn | xx.x (xx.x – xx.x) | nn | xx.x (xx.x – xx.x) | nn | xx.x (xx.x – xx.x) |
| ECBI intensity score | nn | xx.x (xx.x – xx.x) | nn | xx.x (xx.x – xx.x) | nn | xx.x (xx.x – xx.x) |
| SDQ | nn | xx.x (xx.x – xx.x) | nn | xx.x (xx.x – xx.x) | nn | xx.x (xx.x – xx.x) |
| GHQ | nn | xx.x (xx.x – xx.x) | nn | xx.x (xx.x – xx.x) | nn | xx.x (xx.x – xx.x) |
| ASRS (parent) Part A | nn | xx.x (xx.x – xx.x) | nn | xx.x (xx.x – xx.x) | nn | xx.x (xx.x – xx.x) |
| ASRS (parent) Part A | nn | xx.x (xx.x – xx.x) | nn | xx.x (xx.x – xx.x) | nn | xx.x (xx.x – xx.x) |
| PDHS challenging behaviour intensity | nn | xx.x (xx.x – xx.x) | nn | xx.x (xx.x – xx.x) | nn | xx.x (xx.x – xx.x) |
| PDHS challenging behaviour frequency | nn | xx.x (xx.x – xx.x) | nn | xx.x (xx.x – xx.x) | nn | xx.x (xx.x – xx.x) |
| PDHS parenting tasks intensity | nn | xx.x (xx.x – xx.x) | nn | xx.x (xx.x – xx.x) | nn | xx.x (xx.x – xx.x) |
| PDHS parenting tasks frequency | nn | xx.x (xx.x – xx.x) | nn | xx.x (xx.x – xx.x) | nn | xx.x (xx.x – xx.x) |
| CORC-GBO | nn | xx.x (xx.x – xx.x) | nn | xx.x (xx.x – xx.x) | nn | xx.x (xx.x – xx.x) |
| EQ-5D-5L | nn | xx.x (xx.x – xx.x) | nn | xx.x (xx.x – xx.x) | nn | xx.x (xx.x – xx.x) |
| PedsQL psychosocial health summary score | nn | xx.x (xx.x – xx.x) | nn | xx.x (xx.x – xx.x) | nn | xx.x (xx.x – xx.x) |
| PedsQL physical health summary score | nn | xx.x (xx.x – xx.x) | nn | xx.x (xx.x – xx.x) | nn | xx.x (xx.x – xx.x) |
| PedsQL total score | nn | xx.x (xx.x – xx.x) | nn | xx.x (xx.x – xx.x) | nn | xx.x (xx.x – xx.x) |

Table 2.1 Child baseline characteristics (ITT population)

|  |  |  | Randomised intervention | |
| --- | --- | --- | --- | --- |
|  |  | All | PInC | IY |
| Age (years) | N_OBS_ (N_MISS_)  Mean (SD)  Median (IQR)  [Range] | nn (nn)  xx.x (xx.x)  xx.x (xx.x, xx.x)  [xx.x, xx.x] | nn (nn)  xx.x (xx.x)  xx.x (xx.x, xx.x)  [xx.x, xx.x] | nn (nn)  xx.x (xx.x)  xx.x (xx.x, xx.x)  [xx.x, xx.x] |
| Gender | N_OBS_ (N_MISS_)  N(%) Male  N(%) Female | nn (nn)  nn (xx.x)  nn (xx.x) | nn (nn)  nn (xx.x)  nn (xx.x) | nn (nn)  nn (xx.x)  nn (xx.x) |
| Time since diagnosis | N_OBS_ (N_MISS_)  Mean (SD)  Median (IQR)  [Range] | nn (nn)  xx.x (xx.x)  xx.x (xx.x, xx.x)  [xx.x, xx.x] | nn (nn)  xx.x (xx.x)  xx.x (xx.x, xx.x)  [xx.x, xx.x] | nn (nn)  xx.x (xx.x)  xx.x (xx.x, xx.x)  [xx.x, xx.x] |
| Relationship with carer | N_OBS_ (N_MISS_)  N(%) Mother  N(%) Father  N(%) Grand Parent  N(%) Foster Parent  N(%) Other | nn (nn)  nn (xx.x)  nn (xx.x)  nn (xx.x)  nn (xx.x)  nn (xx.x) | nn (nn)  nn (xx.x)  nn (xx.x)  nn (xx.x)  nn (xx.x)  nn (xx.x) | nn (nn)  nn (xx.x)  nn (xx.x)  nn (xx.x)  nn (xx.x)  nn (xx.x) |
| On ADHD medication | N_OBS_ (N_MISS_)  N(%) No  N(%) Yes | nn (nn)  nn (xx.x)  nn (xx.x) | nn (nn)  nn (xx.x)  nn (xx.x) | nn (nn)  nn (xx.x)  nn (xx.x) |
| Time since starting medication | N_OBS_ (N_MISS_)  Mean (SD)  Median (IQR)  [Range] | nn (nn)  xx.x (xx.x)  xx.x (xx.x, xx.x)  [xx.x, xx.x] | nn (nn)  xx.x (xx.x)  xx.x (xx.x, xx.x)  [xx.x, xx.x] | nn (nn)  xx.x (xx.x)  xx.x (xx.x, xx.x)  [xx.x, xx.x] |
| Any other neurodevelopmental diagnoses | N_OBS_ (N_MISS_)  N(%) No  N(%) Yes | nn (nn)  nn (xx.x)  nn (xx.x) | nn (nn)  nn (xx.x)  nn (xx.x) | nn (nn)  nn (xx.x)  nn (xx.x) |

Table 2.2 Parent baseline characteristics (ITT population)

|  |  |  | Randomised intervention | |
| --- | --- | --- | --- | --- |
|  |  | All | PInC | IY |
| Age (years) | N_OBS_ (N_MISS_)  Mean (SD)  Median (IQR)  [Range] | nn (nn)  xx.x (xx.x)  xx.x (xx.x, xx.x)  [xx.x, xx.x] | nn (nn)  xx.x (xx.x)  xx.x (xx.x, xx.x)  [xx.x, xx.x] | nn (nn)  xx.x (xx.x)  xx.x (xx.x, xx.x)  [xx.x, xx.x] |
| Gender | N_OBS_ (N_MISS_)  N(%) Male  N(%) Female | nn (nn)  nn (xx.x)  nn (xx.x) | nn (nn)  nn (xx.x)  nn (xx.x) | nn (nn)  nn (xx.x)  nn (xx.x) |
| Ethnicity | N_OBS_ (N_MISS_)  N(%) White  N(%) Black  N(%) Asian  N(%) Chinese  N(%) Mixed  N(%) Prefer not to say | nn (nn)  nn (xx.x)  nn (xx.x)  nn (xx.x)  nn (xx.x)  nn (xx.x)  nn (xx.x) | nn (nn)  nn (xx.x)  nn (xx.x)  nn (xx.x)  nn (xx.x)  nn (xx.x)  nn (xx.x) | nn (nn)  nn (xx.x)  nn (xx.x)  nn (xx.x)  nn (xx.x)  nn (xx.x)  nn (xx.x) |
| Time since diagnosis | N_OBS_ (N_MISS_)  Mean (SD)  Median (IQR)  [Range] | nn (nn)  xx.x (xx.x)  xx.x (xx.x, xx.x)  [xx.x, xx.x] | nn (nn)  xx.x (xx.x)  xx.x (xx.x, xx.x)  [xx.x, xx.x] | nn (nn)  xx.x (xx.x)  xx.x (xx.x, xx.x)  [xx.x, xx.x] |
| Relationship with child | N_OBS_ (N_MISS_)  N(%) Mother  N(%) Father  N(%) Grand Parent  N(%) Foster Parent  N(%) Other | nn (nn)  nn (xx.x)  nn (xx.x)  nn (xx.x)  nn (xx.x)  nn (xx.x) | nn (nn)  nn (xx.x)  nn (xx.x)  nn (xx.x)  nn (xx.x)  nn (xx.x) | nn (nn)  nn (xx.x)  nn (xx.x)  nn (xx.x)  nn (xx.x)  nn (xx.x) |
| Level of deprivation (SIMD) | N_OBS_ (N_MISS_)  N(%) Q1  N(%) Q2  N(%) Q3  N(%) Q4  N(%) Q5 | nn (nn)  nn (xx.x)  nn (xx.x)  nn (xx.x)  nn (xx.x)  nn (xx.x) | nn (nn)  nn (xx.x)  nn (xx.x)  nn (xx.x)  nn (xx.x)  nn (xx.x) | nn (nn)  nn (xx.x)  nn (xx.x)  nn (xx.x)  nn (xx.x)  nn (xx.x) |
| Education | N_OBS_ (N_MISS_)  N(%) School leaving certificate, Access 1 or 2, National 1 or 2  Standard Grade, GCSE, O Level, …  … | nn (nn)  nn (xx.x)  nn (xx.x)  … | nn (nn)  nn (xx.x)  nn (xx.x)  … | nn (nn)  nn (xx.x)  nn (xx.x)  … |
| Average household income | N_OBS_ (N_MISS_)  N(%) 0 – 11,500  N(%) 11,501 - 33,500  N(%) 33,501 – 150,000  N(%) 150,001 and over | nn (nn)  nn (xx.x)  nn (xx.x)  nn (xx.x)  nn (xx.x) | nn (nn)  nn (xx.x)  nn (xx.x)  nn (xx.x)  nn (xx.x) | nn (nn)  nn (xx.x)  nn (xx.x)  nn (xx.x)  nn (xx.x) |

Table 3.1 Primary outcome - PSOC. ITT population.

|  |  |  | Randomised intervention | |
| --- | --- | --- | --- | --- |
|  |  | All | PInC | IY |
| Baseline | N_OBS_ (N_MISS_)  Mean (SD)  Median (IQR)  [Range] | nn (nn)  xx.x (xx.x)  xx.x (xx.x, xx.x)  [xx.x, xx.x] | nn (nn)  xx.x (xx.x)  xx.x (xx.x, xx.x)  [xx.x, xx.x] | nn (nn)  xx.x (xx.x)  xx.x (xx.x, xx.x)  [xx.x, xx.x] |
| Follow-up | N_OBS_ (N_MISS_)  Mean (SD)  Median (IQR)  [Range] | nn (nn)  xx.x (xx.x)  xx.x (xx.x, xx.x)  [xx.x, xx.x] | nn (nn)  xx.x (xx.x)  xx.x (xx.x, xx.x)  [xx.x, xx.x] | nn (nn)  xx.x (xx.x)  xx.x (xx.x, xx.x)  [xx.x, xx.x] |
| Participants with baseline and follow-up data only | | | | |
| N |  | nn | nn | Nn |
| Baseline | Mean (SD)  Median (IQR)  [Range] | xx.x (xx.x)  xx.x (xx.x, xx.x)  [xx.x, xx.x] | xx.x (xx.x)  xx.x (xx.x, xx.x)  [xx.x, xx.x] | xx.x (xx.x)  xx.x (xx.x, xx.x)  [xx.x, xx.x] |
| Follow-up | Mean (SD)  Median (IQR)  [Range] | xx.x (xx.x)  xx.x (xx.x, xx.x)  [xx.x, xx.x] | xx.x (xx.x)  xx.x (xx.x, xx.x)  [xx.x, xx.x] | xx.x (xx.x)  xx.x (xx.x, xx.x)  [xx.x, xx.x] |
| Change from baseline | Mean (SD)  Median (IQR)  [Range] | xx.x (xx.x)  xx.x (xx.x, xx.x)  [xx.x, xx.x] | xx.x (xx.x)  xx.x (xx.x, xx.x)  [xx.x, xx.x] | xx.x (xx.x)  xx.x (xx.x, xx.x)  [xx.x, xx.x] |
| Linear regression analysis predicting change from baseline from randomised intervention group adjusting for baseline PSOC, child age and gender | | | | |
|  |  | Adjusted mean difference (95% confidence interval) | | p-value |
| IY vs. PInC | | x.xx (x.xx, x.xx) | | x.xxxx |
| Residual standard deviation | | x.xx | |  |

Table 3.2 Primary outcome - PSOC. ITT population with 12-month follow-up.

|  |  |  | Randomised intervention | |
| --- | --- | --- | --- | --- |
|  |  | All | PInC | IY |
| Baseline | N_OBS_ (N_MISS_)  Mean (SD)  Median (IQR)  [Range] | nn (nn)  xx.x (xx.x)  xx.x (xx.x, xx.x)  [xx.x, xx.x] | nn (nn)  xx.x (xx.x)  xx.x (xx.x, xx.x)  [xx.x, xx.x] | nn (nn)  xx.x (xx.x)  xx.x (xx.x, xx.x)  [xx.x, xx.x] |
| Follow-up | N_OBS_ (N_MISS_)  Mean (SD)  Median (IQR)  [Range] | nn (nn)  xx.x (xx.x)  xx.x (xx.x, xx.x)  [xx.x, xx.x] | nn (nn)  xx.x (xx.x)  xx.x (xx.x, xx.x)  [xx.x, xx.x] | nn (nn)  xx.x (xx.x)  xx.x (xx.x, xx.x)  [xx.x, xx.x] |
| Participants with baseline and follow-up data only | | | | |
| N |  | nn | nn | nn |
| Baseline | Mean (SD)  Median (IQR)  [Range] | xx.x (xx.x)  xx.x (xx.x, xx.x)  [xx.x, xx.x] | xx.x (xx.x)  xx.x (xx.x, xx.x)  [xx.x, xx.x] | xx.x (xx.x)  xx.x (xx.x, xx.x)  [xx.x, xx.x] |
| Follow-up | Mean (SD)  Median (IQR)  [Range] | xx.x (xx.x)  xx.x (xx.x, xx.x)  [xx.x, xx.x] | xx.x (xx.x)  xx.x (xx.x, xx.x)  [xx.x, xx.x] | xx.x (xx.x)  xx.x (xx.x, xx.x)  [xx.x, xx.x] |
| Change from baseline | Mean (SD)  Median (IQR)  [Range] | xx.x (xx.x)  xx.x (xx.x, xx.x)  [xx.x, xx.x] | xx.x (xx.x)  xx.x (xx.x, xx.x)  [xx.x, xx.x] | xx.x (xx.x)  xx.x (xx.x, xx.x)  [xx.x, xx.x] |
| Linear regression analysis predicting change from baseline from randomised intervention group adjusting for baseline PSOC, child age and gender | | | | |
|  |  | Adjusted mean difference (95% confidence interval) | | p-value |
| IY vs. PInC | | x.xx (x.xx, x.xx) | | x.xxxx |
| Residual standard deviation | | x.xx | |  |

Table 3.3 Primary outcome - PSOC. PP population.

|  |  |  | Intervention received | |
| --- | --- | --- | --- | --- |
|  |  | All | PInC | IY |
| Baseline | N_OBS_ (N_MISS_)  Mean (SD)  Median (IQR)  [Range] | nn (nn)  xx.x (xx.x)  xx.x (xx.x, xx.x)  [xx.x, xx.x] | nn (nn)  xx.x (xx.x)  xx.x (xx.x, xx.x)  [xx.x, xx.x] | nn (nn)  xx.x (xx.x)  xx.x (xx.x, xx.x)  [xx.x, xx.x] |
| Follow-up | N_OBS_ (N_MISS_)  Mean (SD)  Median (IQR)  [Range] | nn (nn)  xx.x (xx.x)  xx.x (xx.x, xx.x)  [xx.x, xx.x] | nn (nn)  xx.x (xx.x)  xx.x (xx.x, xx.x)  [xx.x, xx.x] | nn (nn)  xx.x (xx.x)  xx.x (xx.x, xx.x)  [xx.x, xx.x] |
| Participants with baseline and follow-up data only | | | | |
| N |  | nn | nn | nn |
| Baseline | Mean (SD)  Median (IQR)  [Range] | xx.x (xx.x)  xx.x (xx.x, xx.x)  [xx.x, xx.x] | xx.x (xx.x)  xx.x (xx.x, xx.x)  [xx.x, xx.x] | xx.x (xx.x)  xx.x (xx.x, xx.x)  [xx.x, xx.x] |
| Follow-up | Mean (SD)  Median (IQR)  [Range] | xx.x (xx.x)  xx.x (xx.x, xx.x)  [xx.x, xx.x] | xx.x (xx.x)  xx.x (xx.x, xx.x)  [xx.x, xx.x] | xx.x (xx.x)  xx.x (xx.x, xx.x)  [xx.x, xx.x] |
| Change from baseline | Mean (SD)  Median (IQR)  [Range] | xx.x (xx.x)  xx.x (xx.x, xx.x)  [xx.x, xx.x] | xx.x (xx.x)  xx.x (xx.x, xx.x)  [xx.x, xx.x] | xx.x (xx.x)  xx.x (xx.x, xx.x)  [xx.x, xx.x] |
| Linear regression analysis predicting change from baseline from randomised intervention group adjusting for baseline PSOC, child age and gender | | | | |
|  |  | Adjusted mean difference (95% confidence interval) | | p-value |
| IY vs. PInC | | x.xx (x.xx, x.xx) | | x.xxxx |
| Residual standard deviation | | x.xx | |  |

Table 4.1.1 Secondary outcome – ECBI problem score. ITT population.

|  |  |  | Intervention received | |
| --- | --- | --- | --- | --- |
|  |  | All | PInC | IY |
| Baseline | N_OBS_ (N_MISS_)  N (%) ≤ 11  N (%) > 11 | nn (nn)  nn (xx.x)  nn (xx.x) | nn (nn)  nn (xx.x)  nn (xx.x) | nn (nn)  nn (xx.x)  nn (xx.x) |
| Follow-up | N_OBS_ (N_MISS_)  N (%) ≤ 11  N (%) > 11 | nn (nn)  nn (xx.x)  nn (xx.x) | nn (nn)  nn (xx.x)  nn (xx.x) | nn (nn)  nn (xx.x)  nn (xx.x) |
| Participants with baseline and follow-up data only | | | | |
| N |  | nn | nn | nn |
| Baseline | N_OBS_ (N_MISS_)  N (%) ≤ 11  N (%) > 11 | nn (nn)  nn (xx.x)  nn (xx.x) | nn (nn)  nn (xx.x)  nn (xx.x) | nn (nn)  nn (xx.x)  nn (xx.x) |
| Follow-up | N_OBS_ (N_MISS_)  N (%) ≤ 11  N (%) > 11 | nn (nn)  nn (xx.x)  nn (xx.x) | nn (nn)  nn (xx.x)  nn (xx.x) | nn (nn)  nn (xx.x)  nn (xx.x) |
| Logistic regression analysis predicting change from baseline from randomised intervention group adjusting for baseline ECBI problem score > 11, child age and gender | | | | |
